## **Aim 3: Test whether the format of survey administration influences the self-reported usability of the survey format**

To test whether the format of survey administration influences self-reported usability of the survey format (Aim 3), we will perform one-way ANOVA to compare overall usability between all four groups. The independent variable in the ANOVA model will be *survey format* (levels: paper non-gamified, web non-gamified (Datacubed Health), web non-gamified (third-party website), and mobile app gamified). We will perform follow-up pairwise comparisons using a Tukey's Honest Significant Difference (HSD) post-hoc test to correct for multiple comparisons and identify the source of any significant *F*-scores from the ANOVAs (i.e. to test whether a significant main effect of app version is driven by differences between the non-gamified paper version vs. non-gamified web versions, non-gamified paper version vs the gamified mobile app version, the Datacubed Health website vs. the third-party website, or the non-gamified web versions vs. the gamified mobile app version). Factor analysis will also be applied to the responses from the usability survey to assess different factors that contribute to the overall usability outcome measure; if stable factors are identified they will be assessed using the approach outlined above.

## **Aim 4: Test whether payment schedule influences retention and compliance.**

To test whether payment schedule influences retention and compliance (Aim 4), we will perform a two-way ANOVA to compare overall retention and compliance between groups (Arms A vs. B vs. C vs. D) and payment schedule (payment biweekly vs. payment at study end). A significant interaction effect is expected, such that differences in retention and compliance between arms will be more pronounced among participants receiving one payment at the end of the study.

### **Aim 5: Test whether gamification of cognitive task administration influences participant experience and technology acceptance.**

To test whether the format of cognitive task administration influences participant experience and technology acceptance, we will compare responses on the usability/TAM surveys between groups (app vs. web task administration) using between subjects t-tests.

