|       |                                      |                                                                                       | 50              | \$5 per completed survey paid at 6 months    |
| Arm D | Electronic: Third-Party website      | No                                                                                    | 50              | \$5 per completed survey, paid every 2 weeks |
|       |                                      |                                                                                       | 50              | \$5 per completed survey paid at 6 months    |

*The secondary objective* of the study is to assess the effect of gamification on participant satisfaction when performing cognitive tasks, as opposed to surveys. Participants who complete any of the initial 6-month cohorts will be recontacted and asked if they would like to continue into an optional, two-week follow-up period. Up to 400 participants will be recruited for this objective. Participants will then be re-randomized in the follow-up period. Participants will be

assigned (1:1) to one of two Arms, E and F. Arm E will examine participant satisfaction with non-gamified, web-based cognitive tasks. Arm F will examine participant satisfaction with gamified, app-based cognitive tasks. Satisfaction will be assessed using a standard, validated instrument, the Technology Acceptance Model (TAM) questionnaire delivered by web or app. Participants will receive \$5 for each completed task or survey after the two-week follow-up period is complete, or up to \$30 in compensation.

| Arm   | Format of task administration | Gamified format?                                                                      | N (Approximate) |
|-------|-------------------------------|---------------------------------------------------------------------------------------|-----------------|
| Arm E | Electronic: Smartphone app    | Yes (opportunity to earn points, create custom avatar, track study progress on a map) | Up to 200       |
| Arm F | Electronic: website           | No (interactive, web-based tasks)                                                     | Up to 200       |

The specific aims of the study are:

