## 8) STUDY ENDPOINTS

The primary outcomes of interest are measures of *retention*, *compliance*, and *usability*.

- *Retention* will be defined as the amount of time participants remain active in the study. Specifically, the primary retention measure will be the number of days between the participant's first assigned study instrument and the date of the last assigned study instrument that they complete.
- *Compliance* will be defined as the number of instruments that the participant fully completes (i.e. responses for all required items) over the course of the study.
- *Usability* will be derived from a survey-based measure that assesses the perceived ease of use and pleasantness of the survey format (see separate attachment). The mean score across items of the survey measure will be used as the primary usability outcome measure of the overall usability of the survey format.

The exploratory outcome measures of interest are measures of *churn*, *engagement*, *activities*, and *routine*:

- *Churn* will be defined as missing more than 25% of assigned instruments within a study phase. Study phases will be defined at the 1 month, 3 month, and 6 month milestones.
- *Engagement* will be assessed based on participant behaviors while using the gamified mobile app (Arm A), and will include the number of clicks on the avatar, number of changes made to the avatar, number of gem store purchases, and the total amount of time spent on the app.
- *Activities* will be defined by classification of clusters of spatiotemporal geolocation data (Arm A).
- *Routine* will be defined by a directed graph model of the *activities*; characteristics will be explored using graph theoretic measures (Arm A).

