### **Arms E and F**

At the end of the initial 6-month participation period, all participants will be asked if they would like to continue into an optional two-week, follow-up period. At the end of this period, participants will be asked if they would like to be contacted about other research opportunities. Participants who complete PEARL study measures, and agree to be contacted, may be contacted in the future, via email, as part of recruitment efforts for other projects.

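### Aim 5 fixes unadjusted t-tests, although original arm and a first-phase usability score could be named as pre-randomisation covariates at little cost

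*Protocol*

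**What the plan says.** The method is in Protocol Section 11, Aim 5: "we will compare responses on the usability/TAM surveys between groups (app vs. web task administration) using between subjects t-tests". Neither that text nor the Aim 5 hypothesis in Section 2 names a covariate.

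The follow-up sample is drawn from the first phase. Section 2 says "Participants who complete any of the initial 6-month cohorts will be recontacted", "Participants will then be re-randomized in the follow-up period", and that they will be "assigned (1:1) to one of two Arms, E and F". On size it says "Up to 400 participants will be recruited for this objective". Section 9, under Arms E and F, words the invitation more widely: "At the end of the initial 6-month participation period, all participants will be asked if they would like to continue into an optional two-week, follow-up".

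A usability score is planned in the first phase. Section 8 says "The mean score across items of the survey measure will be used as the primary usability outcome measure". Section 9 gives all four groups an identical battery in an identical sequence, and Section 11, Aim 3, compares usability across all four. Section 2, Aim 3, expects that score to differ by survey format.

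The Aim 5 questionnaire is described in Section 9: it follows each cognitive task and asks about that task. Section 2, Aim 5, lists usefulness, attitude and intention to use among its outcomes, in addition to ease of use.

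**The concern.** When participants are re-randomised, the trial already holds information that may predict how they will rate the cognitive tasks. It knows which format they used for six months, and it has assigned them a survey on how easy and pleasant that format was. Both precede the second allocation, so adjusting for them cannot introduce bias. In a two-group t-test, any stable difference between people in how they rate study activities stays in the error term.

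What is at stake is the width of the interval for the secondary objective. The follow-up is optional and capped at the 400 people enrolled in the first phase, so precision cannot be recovered by recruiting from elsewhere. Covariates are also best named before the data are seen, because adding them afterwards invites doubt about selection.

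**Working it through.** **Inputs from the protocol.** Unadjusted t-tests, app against web (Section 11, Aim 5). Allocation 1:1, at most 200 per arm (Section 2). The protocol gives no power, effect size, SD or correlation for Aim 5, so there is no figure to reproduce.

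**Assumptions.** Two-sided 5% test, normal approximation, SD = 1, one value per participant. Rho is the correlation between first-phase usability and the TAM score within original arm, varied from 0.1 to 0.7. Any difference in TAM score between original arms is taken as zero; if there is one, adjusting for original arm gains more than is shown here. Uptake is varied from 50 to 200 per arm.

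**Unadjusted test.** Detectable difference at 80% power = (1.960 + 0.842) × √(2/n) = 2.802 × √(2/n).
- n = 200: 2.802 × 0.100 = 0.280 SD
- n = 100: 2.802 × 0.1414 = 0.396 SD
- n = 50: 2.802 × 0.200 = 0.560 SD

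**Adjusted model.** The residual SD is √(1 − rho²). At the difference where the t-test has 80% power, adjusted power = Φ(2.802/√(1 − rho²) − 1.960). For rho = 0.3: 2.802/0.954 = 2.937, and Φ(0.977) = 83.6%.

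| rho | Variance removed | Power | Detectable, n = 200 | Detectable, n = 100 |
|---|---|---|---|---|
| 0 | 0% | 80.0% | 0.280 | 0.396 |
| 0.1 | 1% | 80.4% | 0.279 | 0.394 |
| 0.2 | 4% | 81.6% | 0.274 | 0.388 |
| 0.3 | 9% | 83.6% | 0.267 | 0.378 |
| 0.5 | 25% | 89.9% | 0.243 | 0.343 |
| 0.7 | 49% | 97.5% | 0.200 | 0.283 |

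A gain of five points needs 1 − rho² = (2.802/2.996)² = 0.874, that is rho² ≈ 0.126 and rho ≈ 0.355.

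**Missing usability scores.** If a share m of entrants has no score and the mean is imputed, the variance removed is about rho² × (1 − m). With m = 30%, this is 0.063, 0.175 and 0.343 for rho 0.3, 0.5 and 0.7. Power at 0.28 SD with 200 per arm is then 82.4%, 86.9% and 93.2%.

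**Cost in degrees of freedom.** Original arm takes 3, the usability score 1 and the missing indicator 1, so 5 in all. The table ignores this cost. With k covariates and N participants in total, the variance of the arm difference rises on average by about k/(N − k − 3):
- N = 400: 5/392 = 1.3%
- N = 200: 5/192 = 2.6%
- N = 100: 5/92 = 5.4%

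The model breaks even when rho² = 5/(N − 3), that is at rho of about 0.11, 0.16 and 0.23 respectively. Below those values there is no net gain, and the loss is small.

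**The case against.** The strongest reply is that nothing here is an error. Allocation to the follow-up arms is randomised, so a between-subjects t-test is valid and unbiased, and it contradicts nothing else in the protocol. Covariates are often named in a statistical analysis plan, which is not at hand. The first part stands in full. The second stands only in part, because the protocol does not leave the method open: it names an unadjusted test.

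Three stronger readings are tempting, and the documents support none of them.

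- **That every re-randomised participant already has a usability score.** Section 9 says the instruments are assigned, not that they are completed. The protocol does not say when the usability survey is given or require it for entry. Section 2 recontacts completers, whereas Section 9 invites everyone, and under Section 13 a person who stops returning surveys counts as non-compliant, not withdrawn. Some entrants may have no score.
- **That the two scores measure nearly the same thing.** Ease of use is common to both. However, the first score rates a weekly survey format, which for Arm C is mailed paper and not software, while the second rates a cognitive task and adds further dimensions. The other three arms rated three different platforms.
- **That a material amount of power is lost.** No section supports any value of the correlation. At 0.1 to 0.3 the gain is 0.4 to 3.6 points before the cost in degrees of freedom. Nor does the protocol set a target effect or power for Aim 5 from which a shortfall could be shown.

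These objections limit the size of the point. They do not remove it, because original arm is known for every entrant, the usability survey is planned in all four arms, and using both costs little.

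**Conclusion.** The point holds as a matter of efficiency. The protocol fixes an unadjusted analysis for its secondary objective and leaves unused two pieces of information that precede the second allocation. The t-test is valid, and no conclusion drawn from it would be biased.

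The size is not established. At the t-test's 80% point, adjusted power runs from 80.4% (rho 0.1) through 83.6% (rho 0.3) to 89.9% (rho 0.5), and it is lower if scores are missing. The gain reaches five points only from a correlation of about 0.355, and near 0.1 the extra degrees of freedom cancel it even at full enrolment. These figures rest on the assumed two-sided 5% level, one value per participant and an assumed within-arm correlation. The change is worth making because it is cheap, not because a material loss has been shown.

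**What to change.** In Section 11, Aim 5, replace the t-tests with a linear model for each TAM outcome that would have been t-tested, with one value per participant. The terms are follow-up arm (app against web), original arm (A to D) and, where available, the first-phase mean usability score. Original arm belongs in the model alongside the score because Aim 3 expects the score to differ by format.

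Use only usability scores completed before re-randomisation. Where there is none, impute the original-arm mean and add a missing indicator, so that nobody is dropped. Report the unadjusted difference as a sensitivity analysis.

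The protocol gives the questionnaire after each task and does not say how the responses become one value per participant. The t-test needs that rule as much as the linear model does, so it should be stated in the same place.

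The cost is a few sentences of text, a merge on the coded participant ID and about five degrees of freedom. No new data, participants or procedures are needed.

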#### **4) INCLUSION AND EXCLUSION CRITERIA**

Participants must be 18-89 years of age, reside in the United States, have access to Google Chrome or Safari internet browser (on a computer, tablet, or phone) and email, and be able and willing to complete and return one to two surveys per week. Participants must also own an Android or iOS smartphone (manufactured in 2014 or later) with an operating system capable of supporting the study app (Android 6.0 or greater; iOS 10.0 or greater) and with an active data plan (1GB/month or more). Potential participants will be asked to indicate that they understand English well enough to comprehend the informed consent documents and study instructions. English language abilities will be confirmed using comprehension questions during the consent process (see Section 29). No individuals unable to demonstrate they are capable of giving informed consent in English by correctly answering these questions will be enrolled. During consent, we will ask participants if they have any prior experience with the study smartphone app. Participants who indicate prior experience with the study smartphone app will be excluded from the study and will be considered ineligible.

We will not collect information about pregnancy or exclude subjects based on pregnancy status because the study will only involve use of a smartphone app and no other interventions or procedures. We will not recruit prisoners. We will not recruit minors under the age of 18.

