## **7) STUDY TIMELINES**

Each participant will be asked to complete surveys for six months after enrollment. Over the course of that six-month period, they will receive roughly one survey each week either by mail, within the smartphone app, through the Datacubed Health website, or through a third-party

website. Each survey will last no longer than 10 minutes, but most will be shorter (~3 minutes). A subset of participants who complete the initial six-month period will be given the option to continue into a two-week follow-up period, during which they will complete up to 6 more activities (cognitive tasks and usability/TAM surveys).

We plan to enroll all participants in the study within one year. We plan to complete primary analyses of the study data within two years.

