After 6 months, participants who indicate that they wish to continue with the study will enter an optional two-week, follow-up period. Participants will be randomized to complete activities (cognitive tasks and usability/TAM questionnaires) in the same smartphone app used for the initial 6-month, study period, or using a secure email link. Participants will complete validated, commonly used cognitive tasks assessing working memory and decision-making (e.g., Stroop Task, Wisconsin Card Sort Task, N-Back task, etc.). After completing each cognitive task, participants will complete a brief usability/TAM questionnaire asking about their experience completing the relevant task. Participants in the app group will complete the usability/TAM questionnaire in the app, while participants in the web group will receive a separate secure email link to complete the same questionnaire.

Participants will receive \$5 for each week of the study if the study surveys for that week are completed. For the first cohort of 50 participants in each arm, reimbursements will be processed on a regular schedule (every other week) using PayPal, a third-party electronic payment system. For the second cohort of 50 participants in each arm, reimbursements will be processed once, after 6 months of participants. Participants who complete the optional two-week follow-up will receive \$5 via PayPal for each activity completed, after two-weeks. Participants will need to set up a PayPal account. This will require providing certain PII such as name, email address, and checking account information to PayPal and agreeing to the PayPal's privacy and security policies. DataCubed Health will require minimal PII (name and email address) to send payment to the participants through PayPal. These PII will be handled as described immediately below.

Certain personal identifiable information (PII), such as name, email address, and phone number, will be collected from all participants; mailing addresses will also be collected for participants in the paper group. These data will be used for administrative purposes only (e.g. contacting participants and sending surveys). For security, these data will be encrypted and stored in separate files, which can only be referenced through the anonymous subject ID that is assigned to each participant for the study. These data will be destroyed at the end of the study.

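### Protocol Section 2 defines follow-up Arms E and F in opposite ways, and neither the re-randomisation nor the Aim 5 t-test uses original arm, although former Arm A members already have six months on the study app

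*Protocol*

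**What the plan says.** **Arm definitions.** In the secondary objective (Protocol Section 2), the text states "Arm E will examine participant satisfaction with non-gamified, web-based cognitive tasks" and gives Arm F the gamified app. The table directly below reads "Arm E | Electronic: Smartphone app", marked as gamified, and makes Arm F the non-gamified website.

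**Who enters the follow-up.** Section 2 states "Participants who complete any of the initial 6-month cohorts will be recontacted", so all four original arms feed it, Arm A included. Allocation to E or F is a fresh 1:1 randomisation, and no stratification is mentioned. Section 9 says the activities are done "in the same smartphone app used for the initial 6-month, study period, or using a secure email link".

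**Prior app use.** Section 4 states "Participants who indicate prior experience with the study smartphone app will be excluded from the study and will be considered ineligible".

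**Outcome and test.** Section 9 states "After completing each cognitive task, participants will complete a brief usability/TAM questionnaire asking about their experience completing the relevant task". Section 7 allows up to six activities, tasks and questionnaires together. The analysis in Section 11, Aim 5 is "we will compare responses on the usability/TAM surveys between groups (app vs. web task administration) using between subjects t-tests". It names neither original arm nor a score per participant.

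**The concern.** An arm code with two opposite meanings in one section can carry over into allocation lists, datasets and reports. Anyone working from the letters alone would have an even chance of reading the wrong format.

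The Section 4 exclusion suggests that the sponsor thinks familiarity with the app could affect results. Yet a quarter or more of the follow-up may have that familiarity. Original arm is known for everyone before re-randomisation, but neither the allocation nor the analysis uses it. At stake are some precision and, more importantly, what the Aim 5 estimate means: the effect of gamified tasks on people new to the app, or an average over new and experienced users.

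**Working it through.** The protocol gives no alpha, power, SD or sample-size calculation for Aim 5, so there is no stated figure to reproduce. Two-sided alpha 0.05 and all shifts in SD units below are assumptions.

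**1. Arm labels side by side.**

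| Place | Arm E | Arm F |
|---|---|---|
| Section 2, text | web, not gamified | app, gamified |
| Section 2, table | app, gamified | website, not gamified |
| Section 9 and Section 11 (Aim 5) | letter not tied to a format | letter not tied to a format |

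The first two rows cannot both hold. Sections 9 and 11 speak only of app and web groups.

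**2. Share of former Arm A members.** Section 9 expects about 100 per original arm, so with equal completion the share is 100/400 = 0.25. Completion by arm is not given. If it were 85, 70, 55 and 70% in A, B, C and D (assumed), the share would be 85/(85+70+55+70) = 85/280 = 0.30, with 140 per follow-up arm if every completer joins.

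**3. Validity of the t-test.** With 200 per arm, 25% exposed, a shift of 0.5 SD for exposed people in both groups and no true effect, simulation gives a type I error of 0.048. Re-randomisation keeps the nominal level.

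**4. Precision.** Leaving original arm out adds p(1−p)δ² to the variance: 0.25 × 0.75 × 0.5² = 0.047 on a residual variance of 1. The information lost is 0.047/1.047 = 4.5%, or about 18 of 400 participants.

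The 95% range of the chance imbalance in the former Arm A share is:
- at 200 per arm, 1.96 × √(2 × 0.25 × 0.75/200) = ±8.5 points, with about a 30% chance of a gap of at least 5 points;
- at 140 per arm and a share of 0.304, 1.96 × √(2 × 0.304 × 0.696/140) = ±10.8 points.

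With δ = 0.5 SD, these gaps move the estimate by 0.085 × 0.5 = 0.04 SD and 0.108 × 0.5 = 0.05 SD. The standard errors are √(2/200) = 0.10 and √(2/140) = 0.12 SD, so the movement is less than half a standard error and is already part of it.

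**5. Averaged effect.** If familiarity acts only in the app group, the expected estimate is the effect in app-naive people plus share × shift. With a 0.3 SD effect and a share of 0.25:

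| Shift in app group (SD) | Expected estimate (SD) | Simulated (SD) |
|---|---|---|
| −0.50 | 0.3 − 0.125 = 0.175 | 0.174 |
| −0.25 | 0.3 − 0.0625 = 0.2375 | 0.235 |
| +0.25 | 0.3 + 0.0625 = 0.3625 | 0.365 |
| +0.50 | 0.3 + 0.125 = 0.425 | 0.426 |

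**6. Several TAM forms per person.** The Section 2 pay ceiling gives $30/$5 = 6 activities. If each task has its own form, 6/2 = 3 are TAM forms. With one mean per person, simulated type I error is 0.053, 0.045 and 0.044 at within-person correlation 0.3, 0.5 and 0.7. If all three forms were pooled as independent, the design effect 1 + 2ρ would be 1.6, 2.0 and 2.4. Type I error, 2 × P(Z > 1.96/√DE), would be 0.121, 0.166 and 0.206.

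**7. What a breakdown by original arm can show.** With 50 former Arm A members and 150 others per follow-up arm, the standard error of the difference between their two effects is √(2/50 + 2/150) = 0.23 SD. The difference detectable with 80% power is 2.80 × 0.23 = 0.65 SD, against 2.80 × 0.10 = 0.28 SD for the overall effect.

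**The case against.** The strongest reply is that only the label contradiction is an error and the rest is good practice. Much of this stands.

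- **Letters.** A reader might infer that the swapped letters reverse the Aim 5 result. The analysis does not use them: Section 11 compares app with web, and the hypothesis in Section 2 is stated by format. The risk is miscoding in documents built on the letters.
- **Prior app use.** A reader might infer confounding. Re-randomisation removes it, and the t-test's standard error covers chance imbalance. Where familiarity acts only in the app group, the test rejects more often than 5% with no effect in app-naive people. That is not a false positive, because the average effect in the randomised population is then not zero.
- **The exclusion.** Section 4 applies at study entry. Experience gained within the trial does not plainly breach it; it only shows that exposure was thought to matter.
- **Repeated forms.** A reader might infer a type I error of 12 to 21%. The protocol nowhere says that forms are pooled as independent. A between-subjects test naturally takes the person as the unit, and Section 8 already uses a mean score for the related usability outcome. Twelve tests (3 tasks × 4 scales, family error 1 − 0.95¹² = 46% if independent) is also conjecture: Section 2 lists the scales only as examples, and scores from one person would be correlated. How forms are combined may properly be left to an SAP, which was not available.

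What the reply does not remove is the contradiction in Section 2, and the fact that the planned comparison cannot separate app-naive from app-experienced users although the variable that does so is already recorded.

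**Conclusion.** The Arm E/F contradiction is certain from the text and must be corrected in the protocol. Its practical effect is limited because the contrast is defined by format.

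The omission of original arm is real but moderate. The t-test remains valid. The loss of precision is small (about 4.5% at an assumed 0.5 SD shift and a 25% share). The larger matter is interpretation: an effect of 0.3 SD in app-naive people could be reported as anything from about 0.17 to 0.43 SD if familiarity shifts app scores by up to 0.5 SD either way. These sizes rest on assumed shifts and on an unknown mix of original arms among those who join; the share exceeds 25% if the Aim 2 hypothesis on retention holds.

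Aim 5 is the only test of the secondary objective, and the changes cost almost nothing, so they should be made. The documents do not support calling the planned test biased, invalid or anti-conservative.

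**What to change.** 1. Make the Section 2 text and table give Arms E and F the same content, matching any allocation list already in use, and check other documents that use the letters.
2. Stratify the E/F randomisation by original arm (A, B, C, D). If allocation has already taken place, the adjustment in item 3 still applies.
3. In Section 11, Aim 5, replace the t-tests with one TAM score per participant (mean over completed tasks) in a linear model with follow-up group, original arm and payment schedule. This also confirms the participant as the unit of analysis.
4. Report the app–web effect by original arm through a group-by-original-arm interaction, labelled descriptive given its limited power. This is better than simply dropping former Arm A members, because those from Arms B and D bring six months of web experience that could matter on the other side.

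The cost is a corrected sentence or table, a stratified list and a slightly longer model. No further data or participants are needed.
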